## Abstract

**Background:**

Somatoform disorders are characterized by the presence of multiple somatic symptoms without an organic cause that completely explains their symptoms.

These patients generate a high cost in health services. We aim to evaluate the effectiveness and feasibility of a cognitive-behaviour therapy (CBT) programme, administered in group and individual formats in primary care for patients who are diagnosed with abridged somatization disorder.

**Method/design:**

*Design: *Multicentre, randomized, controlled trial involving 3 groups, one of which is the control group consisting of standardized recommended treatment for somatization disorder in primary care (Smith's norms) and the 2 others, the intervention groups, consisting of cognitive-behavioural therapy (10 sessions) administered in individual format (intervention group 1) or in group format (intervention group 2).

*Setting: *29 primary care health centres in the province of Zaragoza and 3 primary care health centres in the province of Mallorca, Spain.

*Sample: *N = 204 patients, (68 in each of the three groups), aged 18–65 years, able to understand and read Spanish, who fulfil Escobar's criteria of Abridgged Somatization Disorder (SSI 4,6), stable with pharmacotherapy over the previous month, and who will remain stable for the next 3 months in the doctor's opinion, having signed informed consent.

*Intervention: *Control group: Standardized recommended treatment for somatization disorder in primary care (Smith's norms). Intervention group: 10 weekly sessions of CBT, following a protocol designed by [name] group at UMDNJ, USA. There are 2 different treatment conditions: individual and group format.

*Measurements: *Survey on the use of health services, number and severity of somatic symptoms, anxiety, depression, quality of life and clinical global impression. The interviewers will not know which group the patient belongs to (blind). The assessments will be carried out at baseline, post-treatment, 6 months and 12 post-treatment.

*Main variables: *Utilization of health services, number and severity of somatic symptoms.

Analysis: The analysis will be per intent to treat. We will use the general linear models of the SPSS v.15 statistical package, to analyse the effect of treatment on the result variable (utilization of health services, number and severity of somatic symptoms).

**Discussion:**

It is necessary to develop more effective psychological treatments for somatoform disorders. This randomised clinical trial will determine whether cognitive behaviour therapy, both in group or in individual format, is effective for the treatment of these patients.

**Trial registration:**

Current controlled trials ISRCTN69944771

## Background

Somatoform disorders, according to the Diagnostic and Statistical Manual of Mental Disorders [1] are characterized by the presence of multiple somatic symptoms without an organic cause that completely explains their symptoms. This group of disorders include functional somatic syndromes such as fibromyalgia, chronic fatigue syndrome or irritable bowel syndrome, diseases increasingly diagnosed at present [2-4]. The most extreme form of this group is somatization disorder, a chronic and polysimtomatic disorder, which is characterized by at least four unexplained symptoms (two gastrointestinal, one sexual and one pseudoneurological symptoms) [1].

Epidemiological research studies [4,5] demonstrate that somatoform disorders show a prevalence of 0.1–0.2% in the general population and 5% in primary care settings. Although there are no specific studies on the prevalence of undifferentiated somatoform disorder (less restrictive in their diagnostic criteria), it is considered the most common disorder of the group, with a prevalence rate of up to 4.4% in the general population [6] and 22% in primary care settings [7]. In the United States it is estimated that health costs of this group of diseases accounts for 10% of the country's total health care costs [8]. The high percentage of work incapacity of these patients, the use of social services and high psychiatric comorbidity suggest the need to develop systematic research on these disorders [9]. In recent years, an abridged form of somatization disorder, more prevalent than and with the same severity of complications and use of health services as somatization disorder, has been described for research purposes [9].

Somatizing patients mostly attend their primary care physician [7], so a set of recommendations, called "Smith's norms" has been developed for the care of these patients in primary care settings [10,11]. These norms include regular appointments, systematic exploration of the symptoms referred to by the patient, avoidance of unnecessary diagnostic tests and referrals to appropriate mental health specialists, among others. At the pharmacological level, research on specific somatoform disorders are rare, so there is no a solid foundation on which to build reliable pharmacological recommendations [12]. However, studies do exist on the pharmacological treatment of pain (the main symptom of most somatoform disorders). According to these studies, antidepressant drugs (tricyclic antidepressants, mirtazapine, venlafaxine and duloxetine) [13,14] achieved a significative improvement in these disorders. For the psychological treatment, several intervention programmes (both in individual and group formats) have been developed. They are based on psychodynamic psychotherapy [15-17], educational interventions [10,11] and cognitive-behavioural psychotherapy [18-20]. However, there are few studies that evaluate the effectiveness of these interventions [14].

## Methods/design

### Objectives

The general aim is to evaluate the effectiveness and applicability of a programme of cognitive-behavioural therapy (individual and group formats) for Abridged somatization disorder (SSI 4,6) [9] compared with usual treatment.

The specific aims are:

To determine the effectiveness and cost-effectiveness of group compared with individual cognitive-behavioural intervention for patients with Abridged somatization disorder.

To identify the variables that predict greater effectiveness of cognitive-behavioural therapy in somatizing patients.

To determine whether gender differences exist for the variables included in the study.

To assess the influence of work incapacity in the evolution of the symptoms.

### Design

This is a multicentre, controlled trial with a random allocation of patients into three alternative branches (see Figure 1):

**Figure 1 F1:**
[figure not shown]

1. Standard treatment or "Smith's norms" (control group)

2. Individual cognitive-behavioural therapy (CBT) (intervention group 1)

3. Group CBT (intervention group 2).

The evaluation of the treatment outcomes will be performed at patient level and they will be assessed individually.

### Setting and study sample

Patients will be recruited from any of the 29 primary health care centres in the province of Zaragoza and 3 in the province of Mallorca, Spain. Patients will be recruited by doctors working in these primary care centres until the required sample is completed, without a quota of patients assigned for each centre.

Patients considered for **inclusion **are those aged 18–65 years, able to understand and read Spanish, who fulfil Escobar's criteria of Abridged Somatization Disorder (SSI 4,6) [9], stable with pharmacotherapy over the previous month, who will remain stable for the next 3 months in the doctor's opinion, and who have signed informed consent. Those **excluded **will be patients with any primary psychiatric diagnosis other than somatization disorder, severe personality disorder that prevents an adequate implementation of the protocol for evaluation and/or intervention, inability to attend intervention sessions and refusal to participate.

### Intervention

Control group or standardized recommended treatment for somatization disorder in primary care (Smith's norms) [10,11]: standardized letter to the family doctor with Smith's norms that includes: 1. Provide brief, regularly scheduled visits. 2. Establish a strong patient-physician relationship. 3. Perform a physical examination of the area of the body where the symptom arises. 4. Search for signs of disease instead of relying of symptoms. 5. Avoid diagnostic tests and laboratory or surgical procedures. 6. Gradually move the patient to being "referral ready".

Experimental or intervention group: establishment of the protocol developed by [name] et al [22] from the University of New Jersey that includes 10 weekly sessions of treatment and evaluation over 4 designated times: Time 1 (baseline), Time 2 (aftercare), Time 3 (6 months post-intervention), and Time 4 (1 year post-intervention).

There will be two different treatment conditions following the same protocol: individual and group formats. Inclusion in any of the 3 conditions will be random.

- SPPI (Standardized polyvalent psychiatic interview) [21]: Psychiatric interview designed by our group to diagnose psychiatric morbidity in primary care settings [4], that permits DSM-IV and ICD-10 psychiatric diagnosis. If the overall score of any of these sections is equal to or greater than 2, it is considered a positive score in the SPPI and therefore a "psychiatric case".

- Diagnosis of psychiatric or somatic disease. Causal attribution of the symptoms (psychiatric or physical attribution) according to the doctor.

- Anxiety and depression levels assessed by Hamilton Test for Anxiety and Depression (HAM-A and HAM-D) [25,26].

-Clinical global impression (CGI).

- Quality of life assessed by SF-36 (Survey of health and quality of life) [27]: Instrument that explores quality of life related to physical and mental health.

### Statistical methods

#### Sample size

To calculate the sample size we consider that the effectiveness of usual treatment (Smith's norms) is rather low, estimated at about 20% in most of the variables [10,11]. We aim to assess whether the new intervention is at least 20% more effective than usual treatment. Assuming an alpha risk of 0.05 and a beta risk of <0.20 in a bilateral contrast, we would need a sample size of 62 patients with abridged somatization disorder in each group [28]. Furthermore, if we expect a 10% loss, ie, people who do not complete the study period, the necessary sample size would be 68 patients in each group, i.e. a total sample of 204 patients.

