#### Analysis strategy

Analysis will be per intent to treat. First we will compare the two intervention groups (individual and group cognitive-behaviour therapy) and the control group in order to verify that there are no significant differences among them (socio-demographic characteristics, clinical baseline data, etc). We will use the mean (standard deviation) in the continuous variables and percentages in the categorical variables. For comparisons we will use the Kruskal-Wallis test for continuous variables and the Chi-squared test for categorical variables. Non-parametric tests may also be used.

The main variables of the result are SSS, SSQ, SOMS and utilization of healthcare services at 1-year. Process variables include severity of depression (HAM-D) and anxiety (HAM-A), clinical global impression (CGI), quality of life (SF-36), and socio-demographic variables.

We will use the general linear models of the SPSS 15 statistical package, to analyse the effect of the treatment on the continuous result variables (SSS, SSQ and SOMS). We will use the analyses of linear mixed models to analyse the effect of the continuous process variables (depression, anxiety, clinical impression, quality of life).

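### The stated 62 patients per group does not follow from the stated two-sided inputs: for 20% v 40% it gives about 68–70% power, not at least 80%

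*Protocol article*

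**What the plan says.** The Sample size section takes the effectiveness of usual treatment (Smith's norms) as "estimated at about 20% in most of the variables". The target is given in one sentence: "We aim to assess whether the new intervention is at least 20% more effective than usual treatment". The error rates and the result follow: "Assuming an alpha risk of 0.05 and a beta risk of <0.20 in a bilateral contrast, we would need a sample size of 62 patients" in each group. An allowance for 10% loss then leads to the recruitment target: "the necessary sample size would be 68 patients in each group, i.e. a total sample of 204 patients".

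The section gives no effectiveness rate for the intervention and no formula. It does not say which of the possible contrasts among the three groups the calculation serves, and it mentions no one-sided test.

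The Analysis strategy section plans general linear models for "the effect of the treatment on the continuous result variables (SSS, SSQ and SOMS"). The Objectives section has a general aim, CBT in both formats against usual treatment, and a specific aim, group against individual CBT.

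**The concern.** A control percentage, an improvement in percent, alpha, beta and sidedness are the inputs of a standard comparison of two proportions. Put into the usual formulas, they give a number well above 62. The inputs and the result are both printed in the same paragraph, so this is a disagreement within the text and not a detail left to a fuller document.

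This paragraph is the only justification offered for 204 patients. If the power for a 20-point difference is nearer 70% than 80%, about three in ten true effects of that size would be missed in a pairwise comparison, where the plan promises fewer than two in ten. A non-significant result would then be read as stronger evidence against CBT than the design supports.

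**Working it through.** **Inputs from the Sample size section.** Alpha 0.05, two-sided; beta 0.20 as the upper limit; control rate p1 = 0.20; 62 evaluable and 68 recruited per group.

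**Assumed input.** Intervention rate p2 = 0.40, that is, 20 percentage points more. The protocol does not state it.

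**Constants.** z(0.975) = 1.960, z(0.95) = 1.645, z(0.80) = 0.842. Variance terms: p1(1 − p1) + p2(1 − p2) = 0.16 + 0.24 = 0.40; with the mean rate 0.30, 2 × 0.30 × 0.70 = 0.42.

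**1. Trying to reproduce 62 with the stated two-sided test**

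- Unpooled: n = (1.960 + 0.842)² × 0.40 / 0.20² = 78.5, so 79 per group.
- Pooled: n = (1.960 × √0.42 + 0.842 × √0.40)² / 0.20² = 81.2, so 82 per group.
- With continuity correction: 91 per group.

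None of these is 62.

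**2. The same formulas, one-sided**

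- Unpooled: n = (1.645 + 0.842)² × 0.40 / 0.20² = 61.8, so 62.
- Pooled: n = (1.645 × √0.42 + 0.842 × √0.40)² / 0.20² = 63.9, so 64.

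The unpooled one-sided formula returns the printed figure.

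**3. Two-sided power for 20% v 40%**

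| Evaluable per group | Unpooled | Pooled | Exact, uncorrected chi-squared |
|---|---|---|---|
| 62 | 70.2% | 68.5% | 68.9% |
| 68 (no losses) | 74.1% | 72.6% | 73.3% |

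For example, unpooled at 62: 0.20 / √(0.40/62) = 2.490; 2.490 − 1.960 = 0.530; power = Φ(0.530) = 70.2%. The type II risk at 62 is therefore 30–31%. With Fisher's test or Yates' correction, power at 62 is about 62%.

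**4. What 62 per group can detect with 80% power, two-sided**

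- Proportions: 20% v about 43% (pooled formula, p2 = 0.432).
- Means: the normal approximation gives (1.960 + 0.842) × √(2/62) = 0.503 standard deviations; the t-test gives 0.507, about 0.51.

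**5. The relative reading.** If the 20% were relative, the comparison would be 20% v 24%, and about 1,680 per group would be needed. That is nowhere near 62, so the absolute reading is the natural one and the more favourable to the plan.

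**The case against.** The strongest reply is that the calculation may have served a different contrast. The general aim sets a CBT programme in two formats against usual treatment, and the Sample size section speaks of one new intervention. Control against both CBT groups combined (62 v 124, two-sided, mean rate 1/3) has power Φ{[0.20 − 1.960 × √(0.2222 × (1/62 + 1/124))] / √(0.16/62 + 0.24/124)} = 79.9% with pooled variance. The unpooled form gives Φ(0.20 / √(0.16/62 + 0.24/124) − 1.960) = 84.5%. So a two-sided route to roughly the claimed power exists. It does not settle the matter. No section states a combined contrast, and the specific aim of group against individual CBT needs a pairwise comparison. What stands is that the contrast must be named.

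A second reply is that effectiveness may mean percentage improvement on a scale. A standardised difference of 0.5 needs 63 to 64 per group, also close to 62. But the section gives no standard deviation and no standardised effect, so this cannot be confirmed. What stands is that 0.40 is an assumed rate and that the 68–70% depends on it.

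Three stronger readings are tempting, and the document does not support them:

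- A reader might infer that a one-sided test was used. The match at 61.8 is suggestive, but the text says "in a bilateral contrast", and the combined-group route comes about as close (62.2 per arm with pooled variance).
- A reader might infer that the trial as analysed is underpowered for any relevant effect. The symptom scales are analysed as continuous, and 80% power for about 0.51 standard deviations, before any gain from baseline adjustment, may be adequate. The document does not say what difference on those scales matters.
- A reader might count the loss allowance as a further error. 62 × 1.1 = 68.2 and 62 / 0.9 = 68.9, so the dispute is over one patient per group and carries no weight.

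**Conclusion.** The concern holds as a mismatch between stated inputs and stated result. For a pairwise two-sided comparison at 0.05 of 20% v 40%, 80% power needs 79–82 evaluable patients per group. The planned 62 give about 68–70%, and 68 with no losses about 73–74%. The stated limit, "a beta risk of <0.20", is missed by about ten percentage points.

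This rests on three assumptions: the effect is 20 absolute points, the comparison is between two single groups, and no multiplicity adjustment or continuity correction is made. A relative reading, Fisher's test, or alpha of 0.025 for two comparisons with control (about 58% power at 62) would widen the gap. Only the unstated combined-group contrast would close it or nearly so. Where the 62 came from remains unknown.

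**What to change.** Correct the Sample size section and leave enrolment at 68 per group:

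1. State the assumed intervention rate, say that the 20% is in absolute points, and name the contrast to which the calculation applies.
2. Replace the power claim: 62 evaluable patients per group give about 69% power for a pairwise two-sided comparison of 20% v 40% at 0.05, or 80% power for about 20% v 43%.
3. Add the figure that fits the planned analysis of SSS, SSQ and SOMS: 62 per group detect a standardised mean difference of about 0.51 with 80% power, before baseline adjustment.

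The cost is a change of wording and a less favourable stated power. No extra patients and no change of conduct are needed.

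### Minor: after the plan's own 10% loss, 68 patients per group leave about 61 completers, not the 62 it says it needs

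*Protocol article*

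**What the plan says.** The Sample size section of the protocol article builds the target in two steps. The base figure comes first: "we would need a sample size of 62 patients with abridged somatization disorder in each group". The loss allowance follows, with loss defined as non-completion: "if we expect a 10% loss, ie, people who do not complete the study period". The result is that "the necessary sample size would be 68 patients in each group, i.e. a total sample of 204 patients". The Abstract repeats both numbers ("N = 204 patients, (68 in each of the three groups"), and the Discussion repeats the total of 204. No formula is given for getting from 62 to 68.

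**The concern.** When a plan names the number needed after losses and the fraction expected to be lost, the enrolment figure is the first divided by one minus the second, rounded up. The stated 68 is one below that result. A reader of the section would believe that the trial can lose 10% of each group and still have 62 left, and it cannot quite do so. What is at stake is the accuracy of the stated loss margin behind 68 and 204, the headline size of the trial. The same step would also be applied to any revised base figure, and the gap can widen as the base grows.

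**Working it through.** **Inputs**, all from the Sample size section:
- base requirement: 62 per group
- expected loss: 10%, taken here as 10% of those enrolled and equal across groups
- stated enrolment: 68 per group, 204 in total
- for the power illustration only: two-sided alpha 0.05 and control effectiveness about 20%, with the target effect read as 20 percentage points (20% v 40%)

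**Reproducing the plan's figure.** Two routes lead to 68:
- 62 x 1.10 = 68.2, rounded to the nearest whole number: 68
- 62/0.90 = 68.89, truncated: 68

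The document does not show which was used. Neither gives the smallest whole number that meets the requirement.

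**Checking it against the plan's own inputs**
- Expected completers from 68: 68 x 0.90 = 61.2, which is 0.8 below 62.
- Enrolment needed for an expected 62: 62/0.90 = 68.89, rounded up to 69. In total, 3 x 69 = 207.
- Check: 69 x 0.90 = 62.1.
- Loss that 68 can absorb while keeping 62: (68 - 62)/68 = 6/68 = 8.8%.
- Difference in enrolment: 1 per group and 3 overall, or 3/204 = 1.5%.

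**Effect on power.** For two proportions, with the pooled variance under the null, power = Φ{[Δ√n - 1.96√(2p̄(1-p̄))]/√(p1(1-p1) + p2(1-p2))}. Here Δ = 0.20, p̄ = 0.30, 1.96√0.42 = 1.270 and √(0.16 + 0.24) = 0.632.
- n = 62: (1.575 - 1.270)/0.632 = 0.48, power 68.5%
- n = 61.2: (1.565 - 1.270)/0.632 = 0.47, power 67.9%

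The difference is about 0.6 percentage points. For a comparison of means with an effect chosen to give exactly 80% at 62 per group (standardised difference 0.503), power at 61.2 is 79.5%, a difference of 0.5 points.

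**Chance of actually keeping 62.** If patients are lost independently with probability 10%:

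| Enrolled per group | One group keeps at least 62 | All three groups do |
|---|---|---|
| 68 | 0.47 | 0.47³ = 0.11 |
| 69 | 0.61 | 0.61³ = 0.23 |

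The low values in the first row mostly reflect planning to an expected count, which is met only about half the time. They do not measure the size of this slip, because the corrected enrolment also misses in most trials.

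**The case against.** The strongest case against raising this is that it is at rounding level. The 10% is a round planning guess and the control rate is itself only approximate ("estimated at about 20% in most of the variables"), so the inputs hardly separate a loss of 8.8% from one of 10%. That stands, and it is why the point is minor.

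The wording does not say what the 10% is a percentage of. If it is 10% of the 62, that is 6.2, or about 6 patients, and 68 - 6 = 62, so the sentence agrees with itself. This reading is possible. A loss of people who do not complete is more naturally a share of those who enter, and on the other reading the sentence should say so.

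The analysis is also by intention to treat ("Analysis will be per intent to treat"), so a patient who stops is not automatically removed. That softens the practical effect of 61 against 62. It does not reconcile the sentence, because the plan itself defines its allowance by completion.

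A reader might infer that the authors used the wrong formula, multiplying by 1.1 where they should have divided by 0.9. The document does not support this as fact, since truncating the correct quotient gives the same 68. A reader might also take the 0.47 and 0.11 above as evidence of a serious shortfall. They are not, because 69 per group gives only 0.61 and 0.23.

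**Conclusion.** The point holds as a minor arithmetical inconsistency. On the stated 62 and 10%, with the loss taken as a share of those enrolled, 68 per group yields 61.2 expected completers, and the figure that meets the requirement is 69 (207 in total). The gap is under one expected completer per group and less than 1 percentage point of power.

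It would be tempting to conclude that the loss step leaves the trial underpowered. It does not. On the 20% v 40% reading, power at 62 is already 68.5%, against a stated target of at least 80% ("Assuming an alpha risk of 0.05 and a beta risk of <0.20 in a bilateral contrast"). That shortfall comes from the base figure, and moving from 68 to 69 would not repair it. The base figure is a separate question. The completer arithmetic here does not depend on it, nor on how the target effect ("We aim to assess whether the new intervention is at least 20% more effective than usual treatment") is read.

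**What to change.** Keep enrolment at 204 and restate the one sentence in the Sample size section. Either of these wordings is consistent with the figures:
- 68 per group allows for a loss of about 8.8% (6 patients per group), leaving 62.
- With a 10% loss, about 61 completers per group are expected from 68.

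If 62 after a 10% loss is to remain a firm requirement, the figures become 69 per group and 207 in total, and the Abstract and Discussion need the same change.

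If the base figure of 62 is revised, divide the new figure by 0.90 and round up. With a base of 82, for example, 82 x 1.1 = 90.2 would suggest 90, which leaves 90 x 0.90 = 81, whereas 82/0.90 = 91.1 gives 92.

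Restating the sentence needs no extra patients. The only cost is a slightly less favourable statement of the loss the trial can tolerate.
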